### Presentation of the Two Strategies

Figure 4 shows the current strategy put in place by the Ministry of Public Health through the integrated CDI and intervention approaches.

**Figure 4 figure4:**
[figure not shown]
Flow chart of the two strategies. CHW: community health worker; HMM: home-based management of malaria; RDT: rapid diagnosis test.

### Outcome Measures

#### Primary Outcomes

The primary outcomes will be the prevention, diagnosis, and treatment of malaria in children younger than 5 years of age by home caregivers at home as measured by comparing malaria follow-up indicators produced by home caregivers in the intervention area to those produced by CHWs in the control group.

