It is very strategic to use home caregivers (mothers of children for instance) for diagnosis and administration of antimalarial treatment because they are the ones who provide first aid to their children. Community health workers (CHWs) can supplement home caregivers in their work by providing more health education, resupplying household care kits, and seeking better access to medicines. Therefore, a strategy to train home caregivers on the diagnosis and administration of malaria treatment is particularly appropriate for achieving more complete coverage. The goals of the strategy are to ensure the early recognition and prompt and effective response to malaria at home, especially for children younger than 5 years old. This strategy will not only reduce the workload of CHWs, but will also solve the unavailability and distance problem that involves people having to walk to meet the CHW for treatment. The aim of the study is to investigate the impact of a home-based intervention strategy for the prevention, diagnosis, and treatment of malaria in children younger than 5 years. We hypothesize that an intervention aimed at empowering home caregivers can make the prevention, diagnosis, and treatment of malaria in children younger than 5 years at home better than those under the integrated CDI strategy of CHWs.

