### Study Design

The study will use a randomized controlled trial design. The trial was registered with the Pan African Clinical Trial Registry (202003487018009) in South Africa on March 18, 2020. It will be a community-based study examining the impact and effectiveness of the home-based malaria prevention, diagnosis, and treatment of children younger than 5 years by home caregivers (intervention) as compared to the home-based malaria management component of the integrated CDI strategy of CHWs (control). Children younger than 5 years and their home caregivers have been randomly placed into the intervention and control groups after the completion of a census of all households in the area by CHWs. In the intervention group, home caregivers will be trained to perform the RDT and administer the treatment (artesunate-amodiaquine) to children younger than 5 years for prompt and effective management at home. CHWs will be responsible for providing health education and for supplying households with malaria kits. In the control group, children younger than 5 years will be followed up through the malaria indicators produced by CHWs.

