### Data Collection Procedure

Trained interviewers were blinded to group allocation and collected data using pretested questionnaires. For baseline data, a pretested questionnaire was administered to home caregivers on the perception (knowledge, attitudes, and practices) of malaria. This questionnaire will be repeated at the end of the intervention. During the intervention, a structured data collection form will be used and will contain monthly malaria follow-up indicators recorded by home caregivers in the intervention group and the malaria follow-up indicators recorded by CHWs in the control group. The data source for the study will be the malaria register used for the intervention in the Fombap health area and the malaria register used by the CHWs in the Baneghang health area.

In the experimental group (Fombap health area), 6 CHWs were chosen from the Fombap population of 5875 inhabitants, corresponding to 1 CHW per 1000 inhabitants. In each CHW’s zone, the CHW conducted a census of all the households where there is at least one child younger than 5 years and their home caregiver. From this census, children younger than 5 years old and their home caregivers were randomly selected for enrollment in the study. They will be trained in the prevention, diagnosis, and treatment of uncomplicated malaria at home. Malaria kits will be distributed to home caregivers to take care of the children younger than 5 years at home.

With Baneghang health area as the control group, 6 CHWs were also randomly selected from the 9 in the Baneghang health area. In each CHW’s zone, the CHW conducted a census in all the households where there is at least at least one child younger than 5 years and their home caregiver. After the households were identified, children younger than 5 years old and their home caregivers were randomly selected for enrollment in the study. Figure 2 shows the outline of the sampling method for the intervention.

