#### Step 4: The Provision and Management of Malaria Kits

SD Bioline Malaria Ag Pf RDT is used in Cameroon and meets the performance criteria recommended by the WHO [20], while a fixed dose of artesunate-amodiaquine is a combination used as first-line treatment in Cameroon [21]. RDTs and malaria kits will be distributed during the training to all home caregivers, and then the CHWs will take care of replacing kits in households. The malaria kits will be provided to CHWs by the research supervisor according to the need expressed. The support kit will consist of a thermometer, 2 RDTs, a packet of 25 mg/67.5 mg of artesunate-amodiaquine and/or 50 mg/135 mg of artesunate-amodiaquine, a packet of paracetamol, and an algorithm chart for malaria management. In case of any fever above 38ºC in the children younger than 5 years of age as confirmed by the thermometer and without any other sign of gravity, the home caregiver will conduct an RDT of malaria. If the test result is positive, the caregiver will administer the child artesunate-amodiaquine and paracetamol; if the result of the test is negative, the caregiver will take the child to a health center for in-depth exams and treatment for the other causes of fever. For statistical purposes and to replace their kits, home caregivers will inform the CHW of their community by phone of the results of the test and the treatment received by their child. Malaria kits will be distributed free of charge for children younger than 5 years old and this will be purchased from the national provision fund. This study is funded by [name].

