#### Step 6: Monitoring and Evaluation Activities

The monitoring of the activities will be carried out by the research supervisor, the head of the health area, and the researchers to compile and evaluate the work completed on the field. A meeting will be organized twice a month, bringing together the research supervisor and the CHWs to monitor activities. For statistical purposes and to replace their kits, home caregivers will inform CHWs in their community of all suspected malaria cases in the children younger than 5 years, of the result of RDTs, and of the malaria treatment received by the child. Each month, the monitoring indicators produced by the home caregivers will be collected by CHWs for evaluation purposes. An evaluation of the activities will be carried out monthly during the period of intervention.

After the intervention, a descriptive, analytical, and comparative study will be made in the Baneghang and Fombap health areas to compare the two strategies. This evaluation will be based on the HMM follow-up indicators reported by home caregivers in the intervention group and will be compared to those of the CHWs in the control group.

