### The Control Group

The integrated CDI strategy is implemented in 5 health districts in the West Cameroon region, including the Penka-Michel Health District, from which our control health area, Baneghang, was randomly selected for the site of the control group. In this area, the malaria management component of the integrated CDI strategy is carried out by 9 CHWs, 6 of whom were randomly selected for the study. CHWs conducted a census in their respective zone of all the households where there is at least one child younger than 5 years and their home caregivers. After identifying the households, children younger than 5 years old and their home caregivers were randomly selected for enrollment in the study.

Usually, when there is a suspected case of malaria in the community, the patient is taken to the CHW's home. The patient is examined by the CHW to check for uncomplicated malaria. If the test is positive, the CHW conducts an RDT and administers malaria treatment; if the test is negative, the CHW refers these patients and those with severe malaria to the health care center and makes home visits to provide health education to parents.

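### Malaria indicators come from caregivers in one arm and CHWs in the other, so differences in suspected or confirmed proportions mix malaria occurrence, detection and completeness of reporting

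*Protocol article*

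**What the plan says.** Under Primary Outcomes, the protocol article measures prevention, diagnosis and treatment by "comparing malaria follow-up indicators produced by home caregivers in the intervention area to those produced by CHWs in the control group". Study Design says the same of the control group: "children younger than 5 years will be followed up through the malaria indicators produced by CHWs". Data Collection Procedure names two registers as the data source, one used for the intervention in Fombap and the other "the malaria register used by the CHWs in the Baneghang health area".

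The care routes are also described separately.

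- **Intervention.** The caregiver holds a thermometer and rapid tests and tests a child whose temperature exceeds 38 ºC. Step 6 states that "home caregivers will inform CHWs in their community of all suspected malaria cases in the children younger than 5 years". Step 4 ties reporting to resupply: "to replace their kits, home caregivers will inform the CHW of their community by phone of the results of the test".
- **Control.** The Control Group section states: "Usually, when there is a suspected case of malaria in the community, the patient is taken to the CHW", at the CHW's home. The CHW examines the child, with no temperature threshold given. Home visits are mentioned for health education.

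The Introduction gives as one aim of the strategy to "solve the unavailability and distance problem that involves people having to walk to meet the CHW for treatment".

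Data Management and Analysis compares the indicator proportions between groups by chi-square test. One instrument serves both arms: an interview on knowledge, attitudes and practices given at baseline. "This questionnaire will be repeated at the end of the intervention".

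**The concern.** The hypothesis in the Introduction is that prevention, diagnosis and treatment will all be better than under CHWs. A register proportion of suspected or confirmed cases can bear on that only if one knows what moves it. Here the thing that differs by arm, namely who tests the child and where, also determines whether the episode enters the register.

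A higher confirmed proportion in the intervention arm could mean weaker prevention or better detection. A lower one could mean better prevention or caregivers who did not report. The chi-square test cannot tell these apart. The planned multiple imputation does not help, because an unreported episode leaves no visible gap to impute.

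The indicator for confirmed cases given artesunate-amodiaquine has a related limit. It starts from recorded confirmed cases, so a control child who never reached the CHW is absent from numerator and denominator alike. Those children are the ones the access rationale is about.

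**Working it through.** **1. The plan's own figure.** Sample Size Calculation gives p1 = 0.44 (intervention), p2 = 0.33 (control), z = 1.96 and 0.842, and n = 300 per group.

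- Pooled form: n = [1.96·√(2·0.385·0.615) + 0.842·√(0.44·0.56 + 0.33·0.67)]² / 0.11² ≈ 306.
- Simpler form: 2·0.385·0.615·2.802² / 0.11² ≈ 307.
- The stated 300 is within about 3% of both. Allowing 15% nonresponse gives 300·1.15 = 345 or 300/0.85 = 353, consistent with the stated 350.

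The sample size is not at issue. The article does not say which indicator 0.44 and 0.33 refer to; they are used below only as two plausible levels.

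**2. What unequal capture does when the denominator is enrolled children.** Assumptions, none of them in the documents: the same true proportion p in both arms, capture c_I in the intervention arm and c_C in control, children independent. The observed proportions are a = c_I·p and b = c_C·p, so the apparent difference is p·(c_I − c_C). With n = 350 per arm, s0 = √(2·m·(1−m)/n) where m = (a+b)/2, and s1 = √((a(1−a)+b(1−b))/n), the two-sided rejection rate is Φ((a−b−1.96·s0)/s1) + Φ((−(a−b)−1.96·s0)/s1).

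Worked row: p = 0.44, capture 100%/90%. a = 0.440, b = 0.396, s0 = 0.0373, s1 = 0.0373. The first term is Φ((0.044 − 0.0731)/0.0373), about 0.22; the second is negligible.

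| Capture, intervention/control | p = 0.44: difference (points) | rejection | p = 0.33: difference (points) | rejection |
|---|---|---|---|---|
| equal | 0 | 5% | 0 | 5% |
| 100%/90% | +4.4 | 22% | +3.3 | 16% |
| 100%/75% | +11.0 | 85% | +8.3 | 67% |
| 90%/75% | +6.6 | 44% | +5.0 | 31% |
| 80%/75% | +2.2 | 9% | +1.7 | 8% |
| 80%/90% | −4.4 | 22% | −3.3 | 16% |

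A relative capture of 0.33/0.44 = 0.75 reproduces the whole planned contrast with no difference in malaria.

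**3. If the denominator of the confirmed proportion is suspected cases.** The problem becomes who is tested. With true positivity 0.44, and fractions f of malaria fevers and g of other fevers brought forward, the register shows 0.44f/(0.44f + 0.56g):

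- f = 0.9, g = 0.6: 0.396/(0.396 + 0.336) = 0.54.
- f = g: 0.44.
- f = 0.6, g = 0.9: 0.264/(0.264 + 0.504) = 0.34.

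**4. The treated proportion.** Suppose 75% of control cases reach the CHW and 95% of those are treated. The register shows 95%, while CHWs treated 0.75·0.95 = 71% of all cases.

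**5. What a common recall module could detect.** If 10% to 30% of 350 children had fever in the past two weeks (assumed), there are 35 to 105 fevers per arm. By the rejection formula in step 2, 80% power around 50% needs a difference of about 32 points at 35 fevers, 23 at 70 and 19 at 105. Power for 11 points is about 15% at 35 fevers and 36% at 105.

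**The case against.** **Better detection is part of what is being tested.** The trial compares two delivery strategies, and bringing the test into the home is meant to find and treat more cases. This stands. A capture gap is not pure bias, and the differences in the table mislead only if the indicator is read as malaria occurrence. It is also why the same proportions cannot double as evidence on prevention.

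**The article never says that a lower suspected or confirmed proportion measures prevention.** True. It lists these as follow-up indicators under Secondary Outcomes, and the planned 0.44 above 0.33 fits an indicator where higher is better at least as well. But prevention is named among the primary outcomes and is to be measured by comparing these indicators, so the misreading is a natural one.

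**Under-capture in control is an inference.** A reader might conclude that the control register misses cases and that the comparison therefore runs in a known direction. The documents do not support this. The account of children being brought to the CHW describes usual care, the enrolled control children are to be followed by six CHWs who also make home visits, and caregiver telephone reports may be incomplete too. An article's silence on active case finding does not show there is none.

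**CHWs are in both chains, and interviewers are blinded.** CHWs do collect the intervention indicators monthly, but the person who detects and first reports the episode still differs. Blinding is described alongside the questionnaires, whereas the indicators come from registers.

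**A recall module should not replace the registers.** A reader might infer that a common interview ought to become the main comparison. Step 5 argues against that: few fevers, low power, and recall that may itself differ because intervention caregivers are trained and hold thermometers.

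The unstated denominator of the confirmed proportion and the unseen questionnaire items may be settled in a fuller document; no criticism is made of their absence.

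**Conclusion.** The concern holds as a limit on interpretation. The article states affirmatively that the indicators have a different producer in each arm and are tested against each other, and its own description of care shows that the route differing by arm governs whether an episode is recorded. Differences in suspected and confirmed proportions therefore combine occurrence, access or detection, and completeness of reporting. The treated proportion cannot show the access gain.

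Neither size nor direction can be given. In the illustrations, capture gaps of 5 to 25 percentage points with no true difference move the rejection rate from 5% to between 8% and 85%, with either sign. These figures rest on assumed capture, enrolled children as denominator and independent children. The last is a simplification, since 350 children share 203 or 225 caregivers and each arm is one health area; the 5% baseline is thus not this trial's actual error rate.

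It would go too far to call the register comparison invalid or biased towards one arm. It remains a usable comparison of recorded detection and management. This is a worthwhile, inexpensive improvement; confidence is medium.

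**What to change.** 1. **Interpretation.** Keep the register comparison. State that between-arm differences in suspected and confirmed proportions will be read as differences in recorded case detection and management under the two strategies, not as prevention effects or malaria occurrence. State the denominator with each result, and note that the treated proportion applies to recorded confirmed cases only.
2. **Sensitivity analysis.** Vary capture in both arms over a stated range, including ranges that reverse the sign, and report where the conclusion changes.
3. **Supporting comparison.** Add one identical module to the end questionnaire already planned in both arms. For each enrolled child, ask about fever in the past two weeks, whether tested, whether given artesunate-amodiaquine, delay from onset, and place of care. Analyse fever on all enrolled children, and testing and treatment within 24 hours on all reported fevers. Label this as supporting, not main, evidence on access, testing and prompt treatment.

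Cost: items 1 and 2 need only text and a short calculation. Item 3 adds a few questions to an interview already scheduled, with no extra visit. Its drawbacks are low precision, possibly differential recall, and no arm-neutral measure of confirmed malaria, which would need common testing in both arms.

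Home treatment was due to end in May 2020. If data collection has closed, only items 1 and 2 apply.

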#### Secondary Outcomes

The secondary outcomes will be the proportions of malaria follow-up indicators, including the proportion of suspected malaria cases, the proportion of confirmed malaria cases, the proportion of confirmed malaria cases who have received artesunate-amodiaquine, the proportion of children younger than 5 years referred to and who received treatment in health care facilities in the health area, and the proportion of household visits made by CHWs.

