**Conclusions:**

Findings from this randomized controlled trial will contribute to resolving the challenges of severe malaria and to limiting the death due to malaria of children younger than 5 years. This will bring benefits to home caregivers who will know how to promptly diagnose and properly treat malaria in their children at home.

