#### Step 3: The Training of CHWs and Home Caregivers

The selected CHWs will be trained by the research team, and home caregivers will be trained by the research team with the help of the CHWs. The training will be focused on malaria management of children younger than 5 years at home and will include recognizing uncomplicated malaria (base on sign and symptoms), performing malaria RDT, administering artesunate-amodiaquine to children in the case of a positive test, and referring RDT-negative children or those with severe malaria to the health care center. The training process will be based on the training handbook of the Cameroon Ministry of Public Health. The training module of the CHW modified version will be used, as it is simple and has practical demonstrations to enhance understanding. The algorithm used in our study (Figure 3) will be adapted from that used in Senegal [10].

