#### Step 5: The Health Education of Home Caregivers

CHWs will provide health education to the home caregivers concerning malaria prevention measures, the advantages of HMM, and the role of home caregivers in the health care of children. Health education will focus on malaria prevention measures, such as cleaning around the house, the use of insecticide-treated mosquito nets, the use of window screens, the use of insecticides, and the closure of doors and windows before nightfall. CHWs will also explain the concept of home-based prevention and treatment of malaria and the possibility of treating uncomplicated malaria in the community and even in the home. They will also explain that if the diagnosis and treatment of uncomplicated malaria occurs within 24 hours, the condition usually progresses to cure, whereas if early diagnosis and treatment do not occur, the condition can progress to severe malaria and even death. CHWs will provide health education to home caregivers by going door-to-door once a week to at least 5 households and will also go once a month to meetings of women in their area. They will also go to replace the malaria kits in any household that has a suspected case.

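### The referral indicator combines RDT-negative children with severe malaria, so a difference between areas cannot be read as better or worse care, and no listed outcome isolates severe malaria or death

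*Protocol article*

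**What the plan says.** Under Secondary Outcomes the protocol article lists five indicators. Three concern suspected cases, confirmed cases, and confirmed cases given artesunate-amodiaquine. The fourth is "the proportion of children younger than 5 years referred to and who received treatment in health care facilities in the health area". The fifth describes CHW activity: "the proportion of household visits made by CHWs". No denominator is given for the last two. The Primary Outcomes paragraph measures the primary outcome by comparing follow-up indicators between the areas, and these five are the only ones named. Data Management and Analysis plans a chi-square comparison of the indicator proportions between groups.

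The referral rules are these:

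- Fombap (intervention), Step 3: caregivers are trained in "referring RDT-negative children or those with severe malaria to the health care center". Step 4 repeats the first part: "if the result of the test is negative, the caregiver will take the child to a health center for in-depth exams".
- Baneghang (control), The Control Group: after a negative test, "the CHW refers these patients and those with severe malaria to the health care center".

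On visits, Step 5 sets a schedule for Fombap: "CHWs will provide health education to home caregivers by going door-to-door once a week to at least 5 households". It adds a visit to replace the kit wherever there was a suspected case. The Control Group section says that CHWs there also make home visits for health education, but gives no frequency.

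The abstract ends: "Findings from this randomized controlled trial will contribute to resolving the challenges of severe malaria", and goes on to malaria deaths. The Discussion repeats this with the verb softened to may.

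**The concern.** The two groups in the referral item carry opposite messages. More RDT-negative children reaching the health centre means that the algorithm is being followed. More severe malaria reaching it means that more children became seriously ill. The hypothesis in the Introduction is that home care does better than CHW care, and a tested indicator should be able to support or contradict that.

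Severe malaria after home care is also a natural safety observation when lay caregivers hold the tests and drugs. Here it would appear only inside a larger count of RDT-negative referrals. Yet severe malaria and death are what the article says its findings bear on.

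The visit indicator has a related weakness. In Fombap part of its value is an instruction of the study, so a significant difference could show only that the instruction was carried out.

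**Working it through.** The article states no figure for this point. Its sample size (300 per group before non-response) is reproduced at 303 to 307 by standard two-proportion formulas for 0.44 against 0.33, but it does not concern referral or severe malaria.

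**1. Referral read as volume.** Take suspected cases as the denominator (an assumption, since none is stated). Let q be the share of tests that are positive, s the share of positives that are severe, and a the share of RDT-negative children who reach care. With all severe cases referred:

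R = a(1 − q) + qs, and the severe share of referrals is w = qs / R.

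The article gives none of q, s or a. Assumed: q from 0.33 to 0.60, s of 0.05 or 0.10, a = 1.

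| q | s | R | w |
|---|---|---|---|
| 0.33 | 0.05 | 0.67 + 0.0165 = 0.686 | 0.024 |
| 0.33 | 0.10 | 0.67 + 0.033 = 0.703 | 0.047 |
| 0.44 | 0.05 | 0.56 + 0.022 = 0.582 | 0.038 |
| 0.44 | 0.10 | 0.56 + 0.044 = 0.604 | 0.073 |
| 0.60 | 0.05 | 0.40 + 0.03 = 0.430 | 0.070 |
| 0.60 | 0.10 | 0.40 + 0.06 = 0.460 | 0.130 |

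Severe malaria is thus about 2% to 13% of referrals. Two things follow.

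- Doubling s from 0.05 to 0.10 raises R by 0.05q, that is by 1.7, 2.2 or 3.0 percentage points. The same rise comes from better compliance: a must increase by 0.05q / (1 − q), which is 2.5, 3.9 or 7.5 points. The indicator cannot tell these apart.
- With s at 0.05, a difference in test positivity alone (0.33 against 0.44) moves R by 0.686 − 0.582 = 10.4 points, with no difference in how any child was handled.

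**2. Referral read as completion.** With referred children as the denominator, the pooled rate is C = w·c_s + (1 − w)·c_n, where c_s and c_n are the completion rates for severe and RDT-negative children.

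- RDT-negative children carry 87% to 98% of the weight, so C says little about severe malaria.
- If both rates are equal in the two areas but w is 0.024 in one and 0.130 in the other, C differs by 0.106 × (c_s − c_n). For an assumed gap of 20 to 40 points, that is 2.1 to 4.2 points from case mix alone.
- Referral is not the same act in the two areas. In Fombap the caregiver both decides and takes the child. In Baneghang the CHW refers and the family must then go. An RDT-negative child kept at home in Fombap may never be recorded as referred, and would then drop out of the denominator.

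**3. Severe malaria and death.** None of the five listed indicators isolates either. The primary outcome adds none, because it is measured through follow-up indicators of the same kind.

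**4. Visits.** If the weekly target applies to each of the 6 CHWs, then over about 26 weeks (December to May) 6 × 5 × 26 = 780 visits are scheduled in Fombap. Counting one home per caregiver, that is 780 / 203 = 3.8 per enrolled caregiver if only enrolled families are visited, or 780 / 408 = 1.9 if visits are spread over all caregivers found in the census. Kit-replacement visits come on top. No control figure can be computed.

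**5. What a severe-malaria comparison could show.** With 350 children per area and the risk halved, power is about 12%, 19%, 41% and 71% at assumed control risks of 1%, 2%, 5% and 10%, ignoring clustering. It can only be descriptive.

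**The case against.** The best counter-argument is the clause requiring that treatment was received. If the denominator is referred children, the item measures completion, and within one type of patient more completion is better. A condensed article may leave the denominator to the full protocol, and both areas refer the same two groups. This stands in part: a reader might infer that the indicator has no direction at all, and the text does not establish that. But completion still pools two groups, is moved by their mix, and starts from a different act of referral in each area. Settling the denominator would not separate the reasons for referral.

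Three other strong readings are tempting and not supported.

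- A reader might infer that household visits occur or are scheduled only in Fombap. Control CHWs also make them, and silence on their frequency does not show that no schedule exists. Reducing CHW workload is also a stated aim, so describing visits in both areas is reasonable.
- A reader might infer that the article promises an effect on severe malaria and death. It says that findings will or may contribute, which is a statement of impact and not a tested hypothesis. The indicator list is also introduced as non-exhaustive, so an unlisted indicator cannot be ruled out, though none is named.
- A reader might infer that the split needs only data already held. Step 6 lists suspected cases, RDT result and treatment as what caregivers report. Severity and death are not on that list.

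**Conclusion.** The concern holds in this limited form. As written, the referral indicator combines RDT-negative and severe cases in both areas, is to be tested between areas, and enters the primary comparison as one of the named indicators. A difference in it cannot be interpreted as benefit or harm. Severe malaria and death have no listed outcome, although the conclusions point to them. A difference in CHW visits may be no more than the study schedule in Fombap.

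The conclusion on pooling rests on the text alone. The sizes (severe malaria at about 2% to 13% of referrals, and a doubling of severe cases worth 1.7 to 3.0 points) rest on assumed test positivity and severity. The visit figures rest on a per-CHW target and on which homes are visited. None of this stops the trial. It should be changed before the indicators are analysed and the conclusions written.

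**What to change.** Report the referral indicator by reason:

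- (a) RDT-negative children who reached and were treated at a facility, out of all RDT-negative children in the area. This denominator keeps children who stayed at home in the count.
- (b) Severe malaria referrals and deaths per enrolled child, as counts with 95% confidence intervals by area, stated to be descriptive and without any claim of power.

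Report CHW household visits as a process measure in both areas, not as evidence of benefit to children. Limit the statements on severe malaria and death in the abstract and Discussion to what (b) can show.

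The cost is a narrower conclusion and a further tabulation. RDT results are already reported in Fombap, so (a) needs little there beyond confirming facility treatment; the control register should be checked for the same items. Part (b) may need one added register field for severity and death. If follow-up has closed without that field, the report should say so and draw no conclusion on either. No added children and no change to any treatment rule are needed.
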